#### Further Exploratory Analyses

Should we find significant treatment effects of the OTP intervention, we will conduct a series of analyses to develop further evidence that bolsters the inference that the effect is due to the treatment.^[[229]](#endnote-229)^, ^[[230]](#endnote-230)^, ^[[231]](#endnote-231)^ We borrow from methods used in mechanism of treatment research that test whether postulated factors associated with the treatment are also related to the outcome.^[[232]](#endnote-232)^, ^[[233]](#endnote-233)^, ^[[234]](#endnote-234)^ We will test the association between putative mediators and outcomes. For example, the putative mechanism for the OTP intervention is that increased THD will improve retention in care. We will examine the association between THD and retention in care as mediators of the intervention effect. We will also see whether the intervention effect is moderated by characteristics of the population or regional variations. For example, we will also examine variation in intervention impact by region and gender. Any significant moderator effects (e.g., differences in effect size by gender) will suggest that there may be other factors that may account for some of the observed intervention effect. We will also explore variation in effect of the intervention by providers to see if there are moderating effects that suggest variation in treatment implementation. Finally, we will test whether there are lagged treatment effects by introducing interaction terms between treatment and time since intervention start by cohort.^[[235]](#endnote-235)^, ^[[236]](#endnote-236)^ These findings will inform our qualitative study methods. We view these analyses as exploratory since we do not have strong hypotheses regarding the nature of these associations, yet we will use these findings to refine further our interpretation of results and presentation of study findings.

### Analysis of qualitative interviews with OTP leadership, staff, and clients

A concurrent triangulation mixed-methods design will be used such that quantitative and qualitative data collection will occur concurrently and results will be integrated after analysis of each.^[[237]](#endnote-237)^ The semi-structured interviews will be transcribed and analyzed with Atlas.ti to identify key facilitators, barriers, and experiences according to the HEIF constructs using directed content analysis^[[238]](#endnote-238)^ integrated with a framework method.^[[239]](#endnote-239)^ Researchers will make field notes immediately after interviews. We will use the first few interviews to develop the coding scheme, and additional transcripts will be compared to previously coded transcripts to ensure the consistent assignment of codes. As emerging concepts are identified, we will adapt the existing coding structure. Using principles of grounded theory, data collection and analysis will be iterative, with the interview adapted to reflect emerging themes. The research team will review the structure of codes to ensure that it is logical and comprehensive. After the team has reviewed the coding structure and all interviews have been reviewed in depth by two researchers, trained project staff will independently code all transcripts using the final coding scheme. Twenty percent of the transcripts will be double coded to assess inter-coder agreement. Any differences in coding will be discussed and resolved after discussion with the investigators. We also will create an analysis audit trail to document all analytic decisions. Targeted analyses will examine the consistency of the data within sites and identify those themes which appear to discriminate between high and low-performing THD OTPs. When coding is complete, the team will meet to review summaries of the qualitative results and refine hypotheses about the contextual factors and strategies that lead to better outcomes and those that might be barriers to success. For the quantitative results, staff responses will be aggregated across each survey time point and group means and standard deviations will be calculated. Multilevel modeling will be used to examine change over time in survey scores given the nested structure of the data (staff nested within clinics).^[[240]](#endnote-240)^

### Analysis of variation in THD associated with race/ethnicity

The quantitative components of Aim 6 (H4-H6) will be examined by including additional terms in the mixed- effects logistic regression models and in the multilevel discrete-time survival model to incorporate interactions between the intervention effect and patient race/ethnicity. If significant interaction effects are detected, simple main effects of intervention will be estimated for each racial/ethnic group to understand how the intervention effect may vary and to identify any inequities in intervention impact.

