We propose a two-part project to develop then test a multidimensional OTP intervention to address clinical decision making, regulatory confusion, legal liability concerns, capacity for clinical practice change, and financial barriers to THD. The intervention will include OTP THD specific dashboards drawn from multiple State databases. The approach will be informed by the Health Equity Implementation Framework. In year 1, we will employ an explanatory sequential mixed method design to combine analysis of large state administrative databases—Medicaid, treatment registry, THD reporting—with qualitative interviews to refine the intervention. In years 2-5, we will conduct a stepped-wedge trial with 36 OTPs (~10,800 Medicaid clients/yr) randomized to 6 cohorts of a six-month long clinic-level intervention over three years. The trial will test the effects of the intervention on 1) THD; 2) retention in care; and 3) adverse healthcare events. We will specifically examine the effects of the intervention for Black/African American and Latinx clients.

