We will employ GLMM models commonly used in the analysis of stepped-wedge trials. ^[[220]](#endnote-220)^, ^[[221]](#endnote-221)^ The models will take the form: 𝐹(𝜇 )=𝜇+𝛽 +𝛿𝑋 +𝛼 +𝜙 ,𝛼~𝑁(0,𝜏2),𝛾 ~𝑁(0,𝜏2) where 𝛽 is a fixed effect for time, 𝑋 is an indicator for intervention in clinic i at time j (coded 0 for the control condition, then 1 from when intervention begins in the clinic through end of study), and 𝛿 is the treatment effect. The models have random effects for clustering at the clinic and individual patient levels, which are assumed to be normally distributed with mean zero and variances 𝜏2 and 𝜏2 , respectively. We will estimate the 𝛼𝜙 effect of intervention while controlling for secular trends and adjusting for clustering within clinic (𝛼𝑖) and individual (𝜙𝑖𝑘), using mixed effects modeling with binary distribution and logit link. Models will be fit using the *glmmTMB* package using R software.^[[222]](#endnote-222)^, ^[[223]](#endnote-223)^ In the case of H1, the primary outcome will be weekly or greater THD, and the fixed-effects coefficients for the intervention effect, exponentiated, will indicate how the intervention increases the odds of weekly or greater THD. Similar mixed models will consider other THD frequencies as outcomes (i.e., 14-day and 28-day). In the case of H3, the same mixed logistic regression model will be used with any adverse events as the outcome, but a one-side test of non-inferiority (i.e., adverse events are no worse under intervention than under the control condition) will be used.^[[224]](#endnote-224)^ We will use a non-inferiority margin of OR≈1.13, which corresponds to an increase in the prevalence of adverse events from 0.20 under the control condition to 0.22 under intervention. In other words, we will test whether the intervention effect is less than OR≈1.13 in a one-sided test. This is equivalent to obtaining a 95% confidence interval for the intervention odds ratio where the upper limit is less than 1.13.

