## Statistical Power

To estimate power for select outcomes, we used a combination of PASS 2022 and Monte Carlo simulation.^[[241]](#endnote-241)^ Using administrative data to estimate sample sizes and baseline rates (μ), we compute detectable differences for 80% power, α = 0.01, ICC=0.05, and SW-RCT with 6 crossover points, and 6 clinics randomized to start at each crossover point. For 7-day or greater THD (i.e., picking up doses every 7 days or less often), we assume the currently prevalence is 0.45. With 36 clinics and approximately 350 clients observed in each clinic in each six-month period (n≈88,200 total observations), power is 93% to detect a small increase (OR=1.1) in the odds of 7-day or greater THD. This corresponds to an increase from a prevalence of 0.45 under the control condition to .47 after intervention. Even when considering racial/ethnic patient subgroups making up just 10% of clinic clients (n≈35 per site and period), power is 86% to detect a modest increase in the odds of 7-day or greater THD (OR=1.3; an increase from 0.45 to 0.52). To estimate power for non-inferiority on the adverse events outcome, we simulated five thousand datasets from a mixed-effects

logistic regression model with the planned stepped-wedge design with no intervention effect. For each of these simulated datasets, the 95% confidence interval for the intervention effect was estimated. Across the five thousand datasets, the upper limit of the odds ratio was less than 1.13 in 4555 datasets, indicating approximately 91% power for the non-inferiority test. Because power is sufficient to detect small intervention effects for the binary outcomes of 7-day or greater THD and adverse events, it is also sufficient to detect small intervention effects on retention in care.

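### Group-specific intervention effects by race/ethnicity should be reported with intervals whatever the interaction test shows, from a model in which period effects may differ by group

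*Protocol*

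**What the plan says.** Protocol section 8.2.3 extends the mixed logistic and discrete-time survival models with terms "to incorporate interactions between the intervention effect and patient race/ethnicity". It then sets a condition: "If significant interaction effects are detected, simple main effects of intervention will be estimated for each racial/ethnic group". The stated purpose of those estimates is to find inequities in the intervention's impact.

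The Protocol Summary, section 2.1 and section 3 carry no such condition: "We will specifically examine the effects of the intervention for Black/African American and Latinx clients".

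The base model in section 8.2.1 has one time term, which "is a fixed effect for time", shared by all clients. On clustering: "The models have random effects for clustering at the clinic and individual patient levels".

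Section 8.3 assumes "80% power, α = 0.01, ICC=0.05, and SW-RCT with 6 crossover points, and 6 clinics randomized to start at each crossover point". Its one equity figure begins "Even when considering racial/ethnic patient subgroups making up just 10% of clinic clients" (about 35 per site and period) and gives 86% power for an odds ratio of 1.3 on 7-day or greater take-home dosing. No power is given for the interaction.

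**The concern.** The rule in section 8.2.3 and the promise in the summary do not fit together. If the interaction is not significant, the analysis as written yields no intervention effect for any racial/ethnic group. The reader then has no estimate or interval with which to judge whether the intervention helped these clients. A non-significant interaction is compatible both with equal effects and with a modest inequity that the test missed, and only the estimates can tell the two apart.

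A second issue affects the test itself. In a stepped wedge, intervention time is later time. A single period effect removes the secular trend common to all clients but not a trend in the gap between groups. If that gap is already closing or widening for other reasons, an intervention-by-race/ethnicity term fitted alone absorbs part of the change.

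**Working it through.** **Inputs (section 8.3).** 36 clinics; 6 steps, hence 7 six-month periods (36 × 350 × 7 = 88,200, the stated total); 350 clients per clinic-period, split 35 and 315 for a 10% subgroup; ICC 0.05; alpha 0.01, sidedness not stated. On the control rate: "we assume the currently prevalence is 0.45". From p = OR × 0.45 / (0.55 + OR × 0.45), odds ratios of 1.1, 1.2 and 1.3 give 0.4737, 0.4954 and 0.5154.

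**Assumption not in the documents.** The correlation between the two groups' clinic intercepts. Results run from 1 (shared) to 0 (independent).

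**Step 1: the plan's own figures.** Generalised least squares on clinic-period means (Hussey-Hughes model). Total variance is 0.45 × 0.55 = 0.2475, of which 5% lies between clinics. Power = Φ(Δ/SE − 2.576).
- Subgroup, 35 per cell: SE 0.01785; 0.0654/0.01785 = 3.66; power 86.2% (stated 86%).
- All clients, 350 per cell: SE 0.00578; 0.0237/0.00578 = 4.10; power 93.6% (stated 93%).

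Both reproduce at two-sided 0.01. One-sided 0.01 would give 91.0% and 96.2%. The 86% is therefore sound as power for the effect inside the subgroup.

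**Step 2: the gating interaction with the terms section 8.2.3 names.** Two group means per clinic-period, common period effects, a group main effect, the intervention and its interaction with group. The interaction SE is 0.01088 (shared intercepts) to 0.01234 (independent).

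| Subgroup OR vs rest | Δ | Power, shared | Power, independent |
|---|---|---|---|
| 1.2 vs 1.1 | 0.0217 | Φ(1.997 − 2.576) = 28% | Φ(1.761 − 2.576) = 21% |
| 1.3 vs 1.1 | 0.0417 | Φ(3.836 − 2.576) = 90% | Φ(3.382 − 2.576) = 79% |
| 1.3 vs 1.0 | 0.0654 | above 99% | above 99% |

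If the gate were run at 0.05, which the protocol does not say, 1.2 vs 1.1 would pass in 42% to 51% of trials (1.96 in place of 2.576). A separate calculation on the logit scale gives 76% to 87% for a ratio of odds ratios of 1.18 (1.3/1.1) and 24% to 32% for a ratio of 1.1.

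**Step 3: calendar time.** Period k has 6(k − 1) intervention clinics and 6(7 − k) control clinics. Mean intervention period: Σk(k − 1)/Σ(k − 1) = 112/21 = 5.33. Mean control period: Σk(7 − k)/Σ(7 − k) = 56/21 = 2.67. The difference of 2.67 periods × 6 months is 16 months.

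Suppose there is no true interaction and the gap drifts at an assumed rate. With shared intercepts and a common period effect:
- 1 point per year gives a spurious 1.33 points; 1.33/1.088 = 1.23; significant at 0.01 in 9% of trials.
- 2 points per year gives a spurious 2.67 points; 2.67/1.088 = 2.45; significant in 45%.

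With independent intercepts the figures are 12% and 58%. With race/ethnicity-by-period terms the bias is zero and the rate returns to 1%.

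**Step 4: the price of those terms.** The interaction SE becomes 0.0146 (shared) to 0.0189 (independent).
- 1.3 vs 1.1: Φ(0.0417/0.0146 − 2.576) = 61%, falling to 36%.
- 1.2 vs 1.1: 14%, falling to 8%.
- 1.3 vs 1.0: 97%, falling to 81%.

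**Limits.** The calculation uses the clinic-level ICC only. It ignores the patient random effect and any variation in the intervention effect between clinics.

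**The case against.** Testing the interaction before looking at simple effects is a recognised guard against over-reading subgroups. Aim 6 is the last of six, is worded as exploratory, and also draws on client interviews that do not depend on the gate. Fitting the interactions at all goes some way towards the promised examination. These points lower the weight of the concern. They do not remove it: exploratory work is better served by estimates with intervals than by a significance filter, and the interaction result can be shown beside them as the guard.

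Four stronger readings are tempting, and the document does not support them.
- **That the model excludes race-by-time terms.** Section 8.2.3 names only the intervention interaction but gives no full specification. A statistical analysis plan, not available here, could add them.
- **That a spurious inequity is likely.** That needs both the terms to be left out and the gap to drift. The protocol gives no drift rate, and the 1 to 2 points per year used above is an assumption.
- **That the 86% is wrong or mislabelled.** Section 8.3 presents it as power within a subgroup, and it reproduces. It needs no relabelling.
- **That the gate is weak in general, or that a missed test will be reported as no inequity.** For 1.3 against no effect in the rest, interaction power exceeds 99% with the terms named. The protocol nowhere says how a non-significant result will be worded.

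**Conclusion.** The concern holds in a limited form. Section 8.2.3 makes group-specific effects conditional on a significant interaction, against an unconditional promise in the Protocol Summary and sections 2.1 and 3. For a 10% subgroup the gate would pass a modest difference (1.2 vs 1.1) only about 21% to 28% of the time and a larger one (1.3 vs 1.1) about 79% to 90%. This rests on two-sided alpha 0.01, ICC 0.05 and an unknown between-group clinic correlation. The 86% in section 8.3 is right for what it describes but says nothing about the gate.

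The need for group-specific period effects follows from the design, with its 16-month average gap between control and intervention observations. The size of any resulting bias cannot be known from the document. None of this touches the main analysis of take-home dosing. It is a cheap improvement that decides whether the equity aim always yields an interpretable answer.

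**What to change.** 1. In section 8.2.3, drop the condition. Report the intervention effect with its confidence interval for each racial/ethnic group for the H1 to H3 outcomes whatever the interaction p-value, with the interaction estimate and its interval alongside.
2. State that period effects may differ by race/ethnicity in the interaction models, by adding race/ethnicity-by-period fixed effects. In the retention model these are calendar-period terms, additional to the dummies for month since treatment start.
3. Optionally, add to section 8.3 the interaction power or the detectable ratio of odds ratios. For a 10% subgroup at 80% power that ratio is about 1.23 to 1.31 with the period terms and 1.17 to 1.19 without them.

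The cost is wording and a few model terms, with no new data or clinics. The interaction SE widens from about 1.1 to 1.5 points with shared clinic intercepts (from about 1.2 to 1.9 if they are independent), and power for 1.3 vs 1.1 drops to about 36% to 61%. That lower power is a further reason not to make reporting depend on the test.

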## Statistical Power

To estimate power for select outcomes, we used a combination of PASS 2022 and Monte Carlo simulation.^[[241]](#endnote-241)^ Using administrative data to estimate sample sizes and baseline rates (μ), we compute detectable differences for 80% power, α = 0.01, ICC=0.05, and SW-RCT with 6 crossover points, and 6 clinics randomized to start at each crossover point. For 7-day or greater THD (i.e., picking up doses every 7 days or less often), we assume the currently prevalence is 0.45. With 36 clinics and approximately 350 clients observed in each clinic in each six-month period (n≈88,200 total observations), power is 93% to detect a small increase (OR=1.1) in the odds of 7-day or greater THD. This corresponds to an increase from a prevalence of 0.45 under the control condition to .47 after intervention. Even when considering racial/ethnic patient subgroups making up just 10% of clinic clients (n≈35 per site and period), power is 86% to detect a modest increase in the odds of 7-day or greater THD (OR=1.3; an increase from 0.45 to 0.52). To estimate power for non-inferiority on the adverse events outcome, we simulated five thousand datasets from a mixed-effects

logistic regression model with the planned stepped-wedge design with no intervention effect. For each of these simulated datasets, the 95% confidence interval for the intervention effect was estimated. Across the five thousand datasets, the upper limit of the odds ratio was less than 1.13 in 4555 datasets, indicating approximately 91% power for the non-inferiority test. Because power is sufficient to detect small intervention effects for the binary outcomes of 7-day or greater THD and adverse events, it is also sufficient to detect small intervention effects on retention in care.

# Ethics/Protection of Human Subjects

## Ethical Standard

The Principal Investigator will ensure that this study is conducted in full conformity with Regulations for the Protection of Human Subjects of Research codified in 45 CFR Part 46*.*

## Institutional Review Board

The protocol, informed consent forms, recruitment materials, and all participant materials will be submitted to the IRB for review and approval. Approval of both the protocol and consent documents must be obtained before any participant is enrolled. Any amendment to the protocol will require review and approval by the IRB before the changes are implemented to the study. All changes to the consent form will be IRB approved; a determination will be made regarding whether previously consented participants need to be re-consented.

A study closure report will be submitted to the IRB after all research activities have been completed.

## Informed Consent Process

In obtaining informed consent, the study team will comply with applicable regulatory requirements and adhere to 45 CFR Part 46. All consent materials (described below) will receive written approval from the IRB prior to being utilized.

### Consent/Assent and Other Informational Documents Provided to Participants

The consent materials attached to this protocol, which adhere to all required regulatory elements, are as follows:

- Part 1 (Year 1- Aim: Conduct qualitative interviews with leadership and staff of 10 OTPs (5 high and 5 low THD flexibility) on clinical and organizational factors affecting take-home dosing decisions.
  - Provider Interview Guide
  - Provider Key Study Information Form
  - Provider Staff Recruitment Script
  - Provider Verbal Consent
- Part 2 (Years 2-5- Aim: Conduct qualitative interviews with OTP leadership, staff, and clients on attitudes, experiences and behaviors related to the intervention.)
  - Patient Interview Guide
  - Patient Key Study Information Form
  - Patient Verbal Consent
  - Patient Recruitment Flyer
  - Provider Interview Guide
  - Provider Key Study Information Form- Interview Portion
  - Provider Key Study Information Form- Survey Portion
  - Provider Recruitment Email
  - Provider Verbal Consent
  - Provider Staff Measures Quantitative Survey

### Waivers

We are seeking the following waivers:

- Waiver of authorization for the collection of administrative data
- Waiver of consent documentation for provider and patient participation in surveys/interview.

## Consent Procedures and Documentation

Prior to scheduling interviews, we will send key information sheets and verbal consent script to any potential participants. Potential participants can, then, agree to schedule a time to speak and each staff member will be asked to provide verbal consent if they are still willing to participate in the interview. At the beginning of each interview, the interviewer will use the verbal consent script to: explain the purpose, risks, and benefits of the study, address any questions or concerns the participant may have, and obtain the participant’s verbal informed consent to participate in the interview and be audio-recorded. We prefer a verbal consent process as this poses less burden to the participants. It will also allow participants to ask questions before they agree to participate in the study. Because we will be using a verbal consent process, we are requesting a documentation of consent waiver (attached).

